## Abstract

**Background:**

Psychological distress, isolation, feelings of powerlessness, and limited social support are realities faced by temporary migrant live-in caregivers in Canada. Furthermore, they experience multiple barriers in accessing mental health services due to their long work hours, limited knowledge of health resources, precarious employment, and immigration status.

**Objective:**

The Women Empowerment - Caregiver Acceptance & Resilience E-Learning (WE2CARE) project is a pilot intervention research project that aims to promote the mental well-being and resiliency of migrant live-in caregivers. The objectives include exploring the effectiveness of this program in achieving the following: (1) reducing psychological distress (depression, anxiety, and stress); (2) promoting committed actions of self-care; and (3) building mutual support social networks. Further, participants’ satisfaction with the intervention and their perceived barriers to and facilitators of practicing the self-care strategies embedded in WE2CARE will be examined.

**Methods:**

A total of 36 live-in caregivers residing in the Greater Toronto Area will be recruited and randomly assigned to either the intervention or waitlist control group. The intervention group will receive a 6-week web-based psychosocial intervention that will be based on Acceptance and Commitment Therapy (ACT). Standardized self-reported surveys will be administered online preintervention, postintervention, and at 6 weeks postintervention to assess mental distress (Depression, Anxiety and Stress Scale), psychological flexibility (Acceptance and Action Questionnaire), mindfulness (Cognitive and Affective Mindfulness Scale – Revised), and resilience (Multi-System Model of Resilience Inventory). In addition, two focus groups will be held with a subset of participants to explore their feedback on the utility of the WE2CARE program.

**Results:**

WE2CARE was funded in January 2019 for a year. The protocol was approved by the research ethics boards of Ryerson University (REB 2019-036) and the University of Toronto (RIS37623) in February and May 2019, respectively. Data collection started upon ethics approval and was completed by May 2020. A total of 29 caregivers completed the study and 20 participated in the focus groups. Data analyses are in progress and results will be published in 2021.

**Conclusions:**

WE2CARE could be a promising approach to reducing stress, promoting resilience, and providing a virtual space for peer emotional support and collaborative learning among socially isolated and marginalized women. The results of this pilot study will inform the adaptation of an ACT-based psychological intervention for online delivery and determine its utility in promoting mental health among disadvantaged and vulnerable populations.

**International Registered Report Identifier (IRRID):**

DERR1-10.2196/31211

## Introduction

The Canadian Temporary Foreign Worker Program engages workers in sectors such as agriculture, petroleum, home caregiving, and other low-skilled occupations [1-3]. Temporary foreign workers (TFWs) are restricted to work only for the employers designated in their work permits. Most TFWs earn low wages, work long hours without any overtime compensation, live in substandard conditions, and have limited to no access to health care services or employment insurance despite paying into these programs [4-7]. The Caregiver Program, previously known as the Live-in Caregiver Program, is a stream of the Temporary Foreign Worker Program, which engages workers in in-home caregiving [1,8,9]. Despite Caregiver Program reforms in November 2014, which provided caregivers with the option of living outside of their employers’ homes, most caregivers continue to live with their employer due to low wages, inability to afford to live independently, and precarious work permits [5,6,10]. Most caregivers are racialized women from lower- or middle-income countries like the Philippines [2,11]. Live-in caregivers are one of the most vulnerable TFW groups because they live and work in private households where government surveillance remains nonexistent, employees’ privacy is gravely undermined, seclusion is often imposed, and unionization is unattainable [4,12]. TFWs are often the primary source of income for their families in their home country, sending back regular remittances and being compelled to tolerate substandard working and living conditions [4,6]. Although participants in this program are eligible to apply for permanent residency for themselves and their immediate families after 24 months of service, they are not allowed to bring their families to Canada until they become permanent residents, which could take 4 to 10 years [1,8]. In other words, family separation is one of the main requirements for receiving their work permit.

A limited but valuable body of literature examined the mental health of migrant live-in caregivers in Canada [13-16]. These studies reported high psychological distress among live-in caregivers, mainly related to concerns about family at home, an inability to fulfill requests for money, precarious employment and immigration, excessive work demands, lack of privacy, reproaches and abuse from employers, fear of deportation and job loss, feelings of alienation, extreme loneliness, and limited social support [14,15]. Based on caregivers’ reality of high stress and limited free time, it is imperative that they be provided with psychosocial support to reduce stress and promote their resilience.

Acceptance and Commitment Therapy (ACT) is an evidence-based psychological intervention that has proven to be effective in addressing mental and physical health challenges in both clinical and nonclinical populations [17-19]. Web-based ACT has also been found to be effective in addressing health challenges such as distress related to trauma, anxiety, depression, and chronic pain [20-22]. It promotes mental wellness and psychological flexibility by helping participants face their distress while engaging in the pursuit of valued actions such as self-care and other meaningful activities. ACT uses mindfulness-based exercises and experiential exercises to decrease experiential avoidance and to enhance one’s psychological flexibility through advancing six core processes: defusion (observing thoughts as thoughts), acceptance (of experiences of emotions and feelings), contact with the present moment (mindfulness), self-as-context (awareness and self-perspective), values (being clear about what matters), and committed action (based on values) [23,24].

The six ACT core processes can support migrant live-in caregivers in coping effectively with their mental health stress by enabling them to recognize their internal psychological struggles (eg, fusion with ideas and thoughts, avoidance of emotions and feelings) and apply ACT strategies like mindfulness, defusion from unworkable ideas, and engaging in committed action consistent with the value of self-care (eg, engaging in culturally syntonic activities like singing or praying and building social support networks). Given that live-in caregivers work long hours, have extremely limited free time, and lack social support, a web-based intervention offers flexible access while promoting virtual social connection.

This paper presents the study protocol of Women Empowerment - Caregiver Acceptance & Resilience E-Learning (WE2CARE), an internet-based ACT for promoting the mental well-being of migrant live-in caregivers. The study aims to reduce psychological distress (depression, anxiety, and stress) and promote committed actions of self-care. The study protocol received ethical approval from the research ethics review boards of Ryerson University (REB 2019-036) and the University of Toronto (RIS37623).

## Methods

### Study Design

A pilot community-based mixed methods design is used to assess the feasibility and effectiveness of the WE2CARE program. WE2CARE involves two sequential phases: a quantitative component that includes a waitlist randomized controlled trial and a qualitative component that involves focus groups. The waitlist control group will be used as an untreated comparison for the active experimental group to determine if the program had an effect.

### Participants and Recruitment Strategies

A total of 36 participants will be recruited by two community champions (ie, trusted members of the caregivers’ community collaborating with community health organizations serving the TFW population) and a snowball sampling technique. The inclusion criteria will include the following: (1) female adults aged ≥18 years, (2) residing in the Greater Toronto Area, (3) working on a temporary work permit as live-in caregivers, (4) able to speak and read English, (5) have internet access, and (6) able to take part in the 6-week intervention. They will be randomized to either the intervention arm or control arm using a random number generator.

In Phase 2 of our study, we will conduct two focus groups with a subset of participants from Phase 1 who indicate interest in participating. The aim of the focus groups is to gain a deeper understanding about participants’ views of the effectiveness of WE2CARE in promoting mental health, their perceived barriers and challenges in accessing this method of delivery (ie, online), and their recommendations to improve the content and method of delivery of this program.

### Treatment Intervention

#### Overview

The WE2CARE intervention consist of six e-learning modules that cover the ACT processes. Each week, participants are invited to complete an online, self-directed, interactive experiential session on ACT strategies (approximately one hour to complete) and to attend a 90-minute live online videoconference during which group discussions and question-and-answer sessions are facilitated by our research team members to support participants’ ACT practice.

#### Module 1: Reflecting on the Present Journey

This module provides the following: (1) an introductory overview of the course, (2) a guided interactive exercise for participants to reflect on their identity and experience as live-in caregivers, including their current distress and challenges, and the factors that motivate them to continue with their jobs (ie, both the immediate tangible rewards and internal values, such as caring for their families back home), and (3) an introduction to mindfulness as an approach toward all experiences, including psychological suffering.

#### Module 2: Developing Adaptive ACT Strategies to Deal With Distressing Experiences

This module supports participants to achieve the following: (1) recognize all thoughts as thought processes rather than being trapped by their literal content; for example, rather than worrying or arguing back with a thought about one’s uncertain future (“I am going to lose my job soon,” “my life will always be hopeless,” etc), one can mindfully recognize and accept them as thoughts and not reality, and focus on experiencing the here and now (defusion, acceptance, present moment); (2) overcome the tyranny of unhelpful rules or stories that constrict adaptive or valued behaviors (eg, “showing emotions is a weakness,” “I am no longer worthy,” “my needs are not important”) (defusion, acceptance); and (3) cultivate appreciation and gratitude, enabling them to connect to any positive aspects of their experience, however small, that may have been neglected due to fusion with the everyday challenges caused by difficult work conditions (eg, enjoying the sunrise, a cup of tea, a warm bath, fresh air; acceptance, present moment).

#### Module 3: Experiencing the Transcendent Self

This module engages participants in experiential exercises that support them to do the following: (1) reconnect with their former sense of self and identities before becoming a migrant caregiver, including their personal and cultural strengths; (2) defuse from any rigid conceptualized self (ie, being just an objectified migrant caregiver) and become aware through the “observer self” that they are not defined by their memories, their experiences, or labels imposed on them (rather, they are the holders of their lived experiences that continue to change throughout life); and (3) rediscover their strengths, passion, interests, and aspirations, and recognize their capacity to make choices based their values (eg, singing in a choir, attending a community event, choosing a new style of clothing; self-as-context, acceptance, present moment, values).

#### Module 4: Getting in Touch With Values and Meaning

This module engages participants to do the following: (1) explore their values in all domains in their life (self-care, family, friends, career, community, spirituality, etc); (2) evaluate whether their actions are moving toward or away from their values and supporting them to achieve balanced living; and (3) commit to self-care and other actions based on their values (values, committed action, acceptance).

#### Module 5: Building a Supportive Network

This module support participants to accomplish the following: (1) negotiate barriers to self-care by drawing from learned ACT strategies; (2) identify personal and community resources and reconnect with existing supports (eg, church, community associations); and (3) build new supports, such as mutual virtual support networks (values, defusion, acceptance, present moment, committed action).

#### Module 6: Committing to Valued Action

This module supports participants to consolidate their commitment to self-care by doing the following: (1) developing concrete short, intermediate, and long-term plans for self-care and (2) anticipating future barriers and formulating mitigating ACT strategies to sustain a commitment to self-care (committed action, values, present moment).

One of the therapeutic goals of WE2CARE is to motivate participants to engage collectively in building social support networks. The weekly videoconference, which will be cofacilitated by two trained research team members, will provide a viable venue to facilitate and model the development of a virtual community of mutual support, which may continue beyond the project.

A previous ACT intervention study conducted by our team members demonstrated that a participant-driven social support e-network (a closed group on Facebook) was effective in reducing social isolation, promoting community engagement, and strengthening mutual support.

### Data Collection

Informed consent will be obtained prior to data collection. Data will be gathered using both quantitative and qualitative tools, which include self-completed questionnaires and focus groups.

Quantitative data will be captured for participants in the control and intervention groups through self-report instruments that will be administered online pre- and postintervention. The intervention group will also complete the questionnaires 6 weeks postintervention. The survey questionnaires will include the following:

1. The preintervention survey will include sociodemographic and health-related questions.

2. The standardized scales administered preintervention, postintervention, and at the 6-week follow-up will include the following:

The Depression, Anxiety and Stress Scale (DASS-21), a set of three self-report scales (21 items) designed to measure the emotional states of depression, anxiety, and stress.The Acceptance and Action Questionnaire (AAQ-2), a 7-item scale specifically designed to measure the impact of ACT core processes conceptualized as psychological flexibility.The Cognitive and Affective Mindfulness Scale – Revised (CAMS-R), a 12-item measure designed to capture a broad conceptualization of mindfulness not specific to any particular type of meditation training.The Multi-System Model of Resilience Inventory (MSMR-I), which consists of three subscales: internal resilience, pursuits and coping, and external resilience. Each subscale contains 9 self-reported items and indicates where the barriers to one’s resilience lie. These scales have shown good psychometric properties including internal consistency, test-retest reliability, and validity.

3. Participants’ evaluation of the WE2CARE program. Participants’ feedback about the program will be captured through a 12-item questionnaire that elicited their perceptions of the impact the program had on their mental and social well-being and their knowledge of how to access mental health services.

Qualitative data will be obtained through focus groups and interactive entries embedded throughout the 6 online modules, including questions on caregiving burden and factors that promote resilience in Module 1 and weekly valued action data logs on self-care in Modules 2-6.

### Data Analysis Planning

Descriptive statistics will be used to summarize participants’ sociodemographics, self-reported health characteristics, and practices. Both independent and dependent *t* tests will be performed to assess the mean score differences for each outcome measure across and within groups. An independent *t* test will be used to compare mean scores across the intervention and control groups. Paired *t* tests will be used to compare the following: (1) baseline and postintervention outcomes and (2) baseline and 6-week postintervention outcomes among intervention participants.

The number of intervention participants at low risk and at risk for anxiety, depression, and stress will also be compared at baseline, postintervention, and 6 weeks postintervention. The Fisher exact test will be used to determine if the number of intervention participants at risk for anxiety, depression, and stress changed across time. Risk for anxiety, depression, and stress will be assessed using the DASS-21 and AAQ-7. The DASS-21 contains three subscales that assess anxiety, depression, and stress. Those that score at a moderate severity level or above for anxiety, depression, and stress will be considered at risk. The cutoffs for a moderate severity level will be set at 9 for anxiety, 13 for depression, and 18 for stress. Based on the AAQ-7 scoring instructions, a score above 23 is associated with depression or anxiety symptoms.

Linear mixed effects models will be created for each outcome of interest from baseline to postintervention among participants in the intervention and control groups. Each model will include two fixed effects parameters and two random effects parameters, one for the intercept and one for the outcome. The intercept fixed effect represents the typical initial score of an outcome and the outcome fixed effect represents the typical increase or decrease in score from baseline to postintervention.

Participants’ feedback on the 12-item questionnaire will be stratified by study arm allocation and an independent *t* test will be used to determine if there are differences in survey responses by study arm allocation.

Quantitative data will be analyzed using SPSS (version 27; IBM Corp) and R (version 1.2.5003; R Foundation for Statistical Computing) for Windows. A threshold of .05 will be used to determine the level of significance for all *P* values.

Qualitative data include transcripts of the audiotaped focus groups and interactive entries embedded throughout the 6 online modules. Both data-driven inductive and question-driven deductive approaches will be used to analyze the data [25]. Each transcript and responses to each module will be reviewed independently by at least two research team members to generate initial codes, which will be reviewed by all team members and developed into a codebook through discussion and consensus. The team will then organize the coded data into themes (common patterns) and illustrations (unique aspects of experience) for reporting [25]. Integrity of data interpretation will be maintained by following strategies of credibility (member check, peer debriefing) and auditability [26,27].

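### The only arm comparison planned for the standardised scales is a t test with no baseline covariate: valid under randomisation, but less precise than ANCOVA on the same data

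*Protocol article*

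**What the plan says.** The analysis is set out under Data Analysis Planning in the protocol article.

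- **Between arms.** An independent *t* "test will be used to compare mean scores across the intervention and control groups". No covariate is named. The text speaks of differences in mean score and does not say whether post scores or changes from baseline are compared.
- **Within participants.** Paired t tests compare baseline with postintervention outcomes, and "baseline and 6-week postintervention outcomes among intervention participants". The Fisher exact test of risk categories also concerns the intervention arm over time.
- **Mixed model.** "Linear mixed effects models will be created for each outcome of interest from baseline to postintervention among participants in the intervention and control groups". Its terms are fixed: "Each model will include two fixed effects parameters and two random effects parameters, one for the intercept and one for the outcome". The second fixed effect is a change over time: "the outcome fixed effect represents the typical increase or decrease in score from baseline to postintervention".

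Data Collection establishes that the baseline scores exist. Both arms complete "self-report instruments that will be administered online pre- and postintervention", and the four scales are listed under "The standardized scales administered preintervention, postintervention, and at the 6-week follow-up will include the following". The six-week assessment is for the intervention arm only, so postintervention is the one later time point at which the arms can be compared.

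**The concern.** The baseline score of a scale is usually the strongest available predictor of its later score. Here it is collected in both arms but is not a covariate in the one test that compares them. Nothing else in the plan fills the gap. Paired tests and the Fisher test do not contrast arms. The mixed model pools both arms around one intercept and one change over time; fitted separately by arm it would still give only within-arm change.

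The independent t test therefore carries the whole randomised comparison of these scales, and Study Design says the waitlist arm is there to show whether the programme had an effect. With 36 women planned and 29 completing, precision is scarce and chance differences at baseline can be sizeable. Participants and Recruitment Strategies describes allocation by random number generator and no stratification on baseline scores.

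This is not a detail left to a fuller plan: the article names the test and spells out the model's parameters.

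**Working it through.** **Inputs from the protocol article.** Planned sample 36 (Participants and Recruitment Strategies), 18 per arm. Completers 17 intervention and 12 control (Results). Significance threshold .05 (Data Analysis Planning), sidedness not stated.

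**Assumptions.** The article gives no power, effect size, SD or baseline-to-post correlation, so there is no stated figure to reproduce. I assume two-sided alpha 0.05, a true difference d = 0.8 SD, equal SDs at both time points, and a correlation r from 0.4 to 0.7.

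**Step 1: chance imbalance at baseline.** The SD of the baseline difference between arms is √(1/17 + 1/12) = 0.377 SD. The probability of a gap above 0.5 SD in either direction is 2[1 − Φ(0.5/0.377)] = 18% per scale. At 18 versus 18 the SD is √(1/18 + 1/18) = 0.333 SD and the probability is 13%.

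**Step 2: what a gap does to the contrast.**
- Post scores: it shifts by r × gap. A 0.5 SD gap gives 0.5 × 0.5 = 0.25 SD at r = 0.5 and 0.7 × 0.5 = 0.35 SD at r = 0.7.
- Change scores: it shifts by −(1 − r) × gap, an over-correction. A 0.5 SD gap gives −0.25 SD at r = 0.5 and −0.15 SD at r = 0.7.
- ANCOVA: the expected shift is removed.

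**Step 3: variance of the contrast, relative to the post-score t test.** Post score 1; change score 2(1 − r); ANCOVA 1 − r². In large samples ANCOVA is below both for any r strictly between 0 and 1, because 1 − (1 − r²) = r² and 2(1 − r) − (1 − r²) = (1 − r)². For the small sample I multiply the ANCOVA variance by 1 + 1/(N − 4) = 1 + 1/25 = 1.04 for expected imbalance, and take one degree of freedom off (26 instead of 27).

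**Step 4: power at 17 versus 12, noncentral t.** The noncentrality is d divided by the standard error. For post scores it is 0.8/0.377 = 2.12. For ANCOVA at r = 0.5 the standard error is 0.377 × √(0.75 × 1.04) = 0.333 and the noncentrality is 0.8/0.333 = 2.40.

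| Assumed r | Change variance | ANCOVA variance × 1.04 | ANCOVA SE ÷ post SE | Power, post | Power, change | Power, ANCOVA |
|---|---|---|---|---|---|---|
| 0.4 | 1.20 | 0.874 | 0.935 | 53% | 46% | 59% |
| 0.5 | 1.00 | 0.780 | 0.883 | 53% | 53% | 64% |
| 0.6 | 0.80 | 0.666 | 0.816 | 53% | 63% | 71% |
| 0.7 | 0.60 | 0.530 | 0.728 | 53% | 75% | 80% |

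Against the post-score test, ANCOVA cuts the standard error by about 7% (1 − 0.935) to 27% (1 − 0.728).

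**Step 5: sensitivity.** At r = 0.3 the gain over post scores is small: 53% to 56%. With the 1.04 factor, ANCOVA breaks even with the post-score test at r = √(1 − 1/1.04) = 0.20. At the planned 18 versus 18, post-score power is 64.5%, and ANCOVA gives 70.6%, 75.5%, 81.8% and 89.5% at r = 0.4, 0.5, 0.6 and 0.7.

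**The case against.** - **The test is valid.** A reader might infer that an unadjusted t test biases the trial or inflates its type I error. It does not: averaged over randomisations it keeps its level. What remains is lost precision, and a shift conditional on whatever imbalance occurred.
- **The text may mean change scores.** This stands. It would be wrong to state that baseline is ignored, and at r = 0.7 the gain would be 75% to 80%, not 53% to 80%. But a change-score test is no better than the post-score test at r = 0.5 and worse below it, and it over-corrects imbalance.
- **A baseline gap does not pass through in full.** Also right: it carries over by r times its size. The 18% is the chance of the gap, not of an error of 0.5 SD in the result.
- **Not every outcome has a baseline.** The 12-item programme evaluation is also compared by arm with a t test, but it is listed apart from the scales given preintervention. The point covers the standardised scales only.
- **A pilot with an exploratory aim need not optimise efficiency.** The article nevertheless states an effectiveness aim, and a small sample makes precision matter more.
- **Correcting the mixed model would be enough.** True, and it is offered below as an equal alternative; as written, the model does not do it.
- **Data collection is over.** That calls for declaring the change. It does not rule it out.

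**Conclusion.** The point holds as a matter of efficiency for the four standardised scales. The one planned arm contrast has no baseline covariate, and no other analysis in the plan supplies an adjusted one. At 17 versus 12, for d = 0.8 SD and r between 0.4 and 0.7, ANCOVA adds about 6 to 27 percentage points of power over a post-score test (59 − 53 to 80 − 53) and 13 to 5 points over a change-score test (59 − 46 to 80 − 75). Both d and r are assumptions, and the gain is slight if r is near 0.3.

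The documents do not support calling the planned test invalid, and they do not settle which scores it compares. Nor would adjustment cure selective loss: 6 of 18 controls withdrew, and ANCOVA handles only the resulting imbalance in the measured baseline score. The change is worth making because the data are already in hand.

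**What to change.** For each standardised scale, replace the independent t test with ANCOVA of the postintervention score on arm and the baseline score of that scale. Report the adjusted mean difference with its 95% CI.

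Alternatively, give the planned mixed model time and arm-by-time terms with a common baseline mean, and report the arm-by-time estimate with its 95% CI. This targets the same contrast and keeps participants with one missing assessment, on the usual missing-at-random assumption. An unstructured covariance for the two time points suits it, since two scores per woman cannot separate a random change from residual error.

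Leave the 12-item feedback comparison as it is. State that the change was made after data collection.

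The cost is one degree of freedom and revised wording, with no new participants or measurements. Complete-case ANCOVA would leave out the one intervention participant without a baseline questionnaire, who is already outside the 17 completers; the mixed model could include her if she gave postintervention data.

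### Within-arm before-after tests, including a 6-week comparison with no controls, carry the same .05 status as the randomised comparison and cannot show that the programme worked

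*Protocol article*

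**What the plan says.** Study Design gives the control arm a clear purpose: "The waitlist control group will be used as an untreated comparison for the active experimental group to determine if the program had an effect".

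Data Collection says that both arms complete "self-report instruments that will be administered online pre- and postintervention", and then adds: "The intervention group will also complete the questionnaires 6 weeks postintervention". Controls therefore have no scheduled score at 6 weeks. The abstract's Methods paragraph does not state this limit: "Standardized self-reported surveys will be administered online preintervention, postintervention, and at 6 weeks postintervention".

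Data Analysis Planning has one test of the outcome scales that is described as a comparison of arms, an independent *t* "test will be used to compare mean scores across the intervention and control groups". It does not give the time point, or say whether scores or changes are compared. Next come two paired comparisons: baseline against postintervention, and "baseline and 6-week postintervention outcomes among intervention participants". A further test of the at-risk counts is also confined to one arm: "The Fisher exact test will be used to determine if the number of intervention participants at risk for anxiety, depression, and stress changed across time". A threshold of .05 applies to every P value. The section does not rank these analyses.

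**The concern.** The arms are randomised so that whatever would have changed anyway can be subtracted. A paired *t* test in the intervention arm asks only whether the mean score moved. It cannot say whether the programme moved it. Outcomes are self-reported, and Results dates data collection from November 2019 to May 2020. Any general shift in distress over that time enters the paired difference in full.

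Since all tests share one threshold and none has priority, a significant paired result beside a non-significant between-arm result could be reported as effectiveness. At 6 weeks the risk is greater, because the data contain no control scores to check against. A reader of the abstract alone could also suppose that the 6-week survey covers both arms.

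**Working it through.** **Inputs from the article.** 36 participants, 18 per arm. Completers: 18 − 1 = 17 intervention and 18 − 6 = 12 control, total 29, as Results states. Threshold .05, taken as two-sided because the article does not say. The article derives no power, effect size or error rate, so there is no design figure to reproduce.

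**Assumed inputs.** The article gives neither a natural change nor a pre-post correlation. I take a natural change δ of 0.2, 0.3 or 0.5 SD of the score and a correlation ρ of 0.5 to 0.7, with equal SDs at both times and no programme effect.

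**Paired test, intervention arm, n = 17.**
- SD of the change, in score SDs: √(2(1 − ρ))
- Standardised change: d_z = δ / √(2(1 − ρ))
- Noncentrality: λ = d_z × √17
- Critical value on 16 df: 2.120
- Probability of significance: P(|T| > 2.120), with T noncentral *t* on 16 df and noncentrality λ

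Example, δ = 0.3 and ρ = 0.5: the SD of the change is 1, d_z = 0.3, λ = 0.3 × 4.123 = 1.237, and the probability is 21%.

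| Natural change | ρ = 0.5 | ρ = 0.6 | ρ = 0.7 |
|---|---|---|---|
| 0 | 5% | 5% | 5% |
| 0.2 SD | 12% | 14% | 17% |
| 0.3 SD | 21% | 26% | 32% |
| 0.5 SD | 49% | 58% | 71% |

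The test is two-sided, so the rates are the same for either direction of change. Natural improvement would look like benefit. Natural worsening would look like harm, or hide a real benefit.

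**Between-arm test, 17 against 12.** If both arms shift by the same δ, it cancels from the difference in means. In 40,000 simulated trials per setting (ρ = 0.5, postintervention scores), the independent *t* test was significant in 4.8% to 5.1% of trials for natural changes from 0 to 0.8 SD. This assumes equal natural change in both arms and dropout unrelated to outcome. The second assumption needs care: 6 of 18 controls (33%) withdrew, against 1 of 18 intervention participants (6%) who did not complete the baseline questionnaire.

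**6 weeks.** The matching calculation cannot be done, because no control scores are collected then.

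**The case against.** The strongest reply is that the plan does contain a randomised comparison. The independent *t* test is listed, Study Design assigns the question of effect to the waitlist arm, and nowhere does the article say that effectiveness will be concluded from the paired tests. A reader might infer that effectiveness rests only on before-after tests; the text does not support that. What remains is that the two kinds of test have equal standing, and that the between-arm test cannot reach 6 weeks.

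A second reply concerns grammar. The phrase restricting the paired tests to intervention participants may apply only to the 6-week comparison, so the postintervention paired test might be run in both arms. That is possible. The restriction is certain at 6 weeks and only the likeliest reading at postintervention. Separate paired tests in each arm would still not compare the arms.

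Third, one-arm follow-up after the controlled period is usual in a waitlist design, and Data Collection discloses it. That is fair. The abstract is incomplete on this point, but it does not claim a randomised comparison at 6 weeks.

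Two further inferences should be resisted. Regression to the mean is not an obvious cause here, because the inclusion criteria set no distress threshold. Nor can one say that untreated control scores near 6 weeks were obtainable, because the article gives no dates for the cohorts' follow-up or for the controls' start.

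Finally, this is a pilot. That lowers the weight of the point, but the article still states effectiveness as an aim.

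**Conclusion.** The point holds, with moderate weight. The paired tests in the intervention arm, certainly the one at 6 weeks and probably the one at postintervention, cannot separate a programme effect from natural change, yet they stand level with the randomised comparison at .05. With no programme effect they would be significant in about 12-17%, 21-32% or 49-71% of trials under a natural change of 0.2, 0.3 or 0.5 SD. These figures rest on the assumed change and correlation. With no natural change the rate is the nominal 5%. The structural point, that 6-week results have no concurrent control, rests on no assumption.

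**What to change.** 1. State that effectiveness is judged only by the between-arm comparison at postintervention, preferably adjusted for the baseline score.
2. Report the paired comparisons and all 6-week results with confidence intervals, as uncontrolled change or maintenance in the intervention arm, and make no effectiveness claim from them.
3. State in the abstract that the 6-week survey is completed by the intervention arm only, in line with Data Collection.

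A 6-week control questionnaire is no longer an option: data collection is complete and the controls have received the programme. The article says that analysis is still in progress, so these changes can be made now. They cost wording and analysis labels, and no new data. The downside is a less favourable headline for the within-arm and 6-week results.
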